## Abstract

Human language permits us to call to mind objects, events, and ideas that we cannot witness directly. This capacity rests upon abstract verbal reference: the appreciation that words are linked to mental representations that can be established, retrieved and modified, even when the entities to which a word refers is perceptually unavailable. Although establishing verbal reference is a pivotal achievement, questions concerning its developmental origins remain. To address this gap, we investigate infants’ ability to establish a representation of an object, hidden from view, from language input alone. In two experiments, 15-month-olds (*N* = 72) and 12-month-olds (*N* = 72) watch as an actor names three familiar, visible objects; she then provides a novel name for a fourth, hidden fully from infants’ view. In the Semantic Priming condition, the visible familiar objects all belong to the same semantic neighborhood (e.g., apple, banana, orange). In the No Priming condition, the objects are drawn from different semantic neighborhoods (e.g., apple, shoe, car). At test infants view two objects. If infants can use the naming information alone to identify the likely referent, then infants in the Semantic Priming, but not in the No Priming condition, will successfully infer the referent of the fourth (hidden) object. Brief summary of results here. Implications for the development of abstract verbal reference will be discussed.

## Introduction

Language is among our most powerful tools for learning and communication. It permits us to learn information that does not, or cannot, manifest perceptually at the time of learning [1], such as historic facts, hypothetical scenarios, or scientific constructs. From toddlers hearing words for absent and often unknown objects (e.g., “Daddy outside is fixing the *trellis*”) to physicists conversing about gravity, the communicative power of language enables us to transmit new information across space and time. This capacity rests upon an appreciation that language can convey information that is decoupled from the here-and-now. This uniquely human power is enabled by *abstract verbal reference*–an appreciation that words are linked to mental representations that can be established, retrieved and modified, even when the entities to which they refer are not perceptually available [2–4]. How, and how early, do infants gain this appreciation?

Evidence documenting infants’ ability to comprehend *displaced (or fragmented) reference* (an operational definition of abstract verbal reference, which entails reference to objects or events that were recently visible but subsequently removed from infants’ view) provides valuable insight into these questions. A nascent appreciation of displaced, or fragmented, reference appears to be present by 12 months of age. Infants interpret pointing gestures as referential [5,6] and refer to a recently hidden entity by pointing to its previous location [7–12]. In addition, 12-month-olds understand that words can refer to recently hidden objects [13–15]. By 14 months, infants bring greater social knowledge to bear, responding to a speaker’s verbal request for an absent object by selecting an object that a speaker prefers [16]. Infants at 14 months also use words to retrieve memories of past events [17]. They remember properties of named, but absent, objects [18] and produce communicative behaviors towards the location of recently hidden objects [19].

In each of these preceding instances, 12-to-14-month-olds’ resolution to the puzzle of displaced reference hinges upon their use of recent visual “anchors”–reminders that scaffold their representation of the now-absent referent [20]. By 16 months, infants go further, successfully resolving displaced reference on the basis of verbal testimony alone [21], even if the absent entity has not previously been “anchored” within the context of the experiment [22]. However, in each of these studies, infants can rely on existing knowledge, acquired when those entities *were* visible.

What remains unknown is when infants successfully acquire *new representations and update them on the basis of language alone*. This is the signature of abstract verbal reference. We propose that if infants can establish a mental representation for the meaning of a novel word from language alone and later draw on that representation to identify a candidate referent of that novel word, this will constitute clear evidence for abstract verbal reference.

There is considerable evidence that 19- to 24-month-old infants resolve abstract verbal reference and successfully infer the meanings of novel words on the basis of linguistic information alone, in the absence of any visual referents [23–26]. For example, Ferguson et al. [2014; 27], showed that 19-month-old infants successfully identify the referent of a novel word even if that referent is not available when the name is introduced. In their study, 15- and 19-month-olds were presented with novel nouns that were arguments of known verbs, either animacy-selecting (“The dax is crying”) or animacy-neutral predicates (“The dax is right there”). When the novel word was presented in linguistic constructions that specified animate arguments, 19-month-olds (but not 15-month-olds) successfully mapped the novel word to an animate object when it later became visible.

But why did 15-month-olds fail? The reviewed literature suggests that between 14 and 16 months, infants can resolve reference to absent objects. On possibility is they cannot yet establish new mental representations for novel words based on linguistic information alone. However, it is also possible that they do have the requisite linguistic and conceptual capacities, but that their relatively sparse lexical knowledge masks them (on average, infants in Ferguson et al. comprehended 4.3 verbs from the MacArthur Level II Short Form). For example, in Ferguson’s task, infants were required to infer the meaning of a novel noun based on a known verb. Infants’ verb knowledge at 15 months may have been too sparse to support the acquisition of novel noun arguments.

We therefore introduce a new paradigm that taps into infants’ capacity for abstract reference, but relies instead on the nouns they know [on average, 15-month-olds comprehend 71 nouns; 28] and their emerging sensitivity to semantic neighborhoods [29,30]. We ask whether priming a sematic neighborhood supports infants’ ability to establish a representation for the referent of a *novel* noun, even when the referent cannot be seen. At issue is [1] how early infants successfully resolve abstract verbal reference, as measured by their ability to acquire novel word meanings from language alone, and [2] whether semantic priming is supports such learning.

## Experiment 1

The goal is to assess whether 15- to 16-month-olds can successfully establish a representation of a novel word’s meaning from language input alone, and recruit this representation later to identify a referent of the novel word. We focused on infants aged 15–16 months because although there is ample evidence that they successfully resolve displaced reference for known words [16,18,22,27,31], there is no evidence that they learn novel word meanings without a referent being present.

### Method

The proposed work conforms with the US Federal Policy for the Protection of Human Subjects and Northwestern University Human Research Protection Program requirements. All research personnel have completed the required responsible conduct of research training and has been certified by the Collaborative Institutional Training Initiative. A protocol amendment that extends the scope of the protocol to include the proposed procedure was submitted and approved by the Institutional Review Board of Northwestern University. This research will be conducted based on caregivers’ written consent and participants’ willingness to complete the experiments. All participants will receive compensation, regardless of successfully completing the experiments.

#### Participants

Seventy-two (*N* = 24 per condition) infants from the Chicago area will be recruited from the laboratory database. Infants will have no more than 15% exposure languages other than English. Caregivers will complete a MacArthur Short Form Vocabulary Checklist: Level II [Form A; 32], augmented with words used in the experiments but not included in the form (see S1 Appendix). They will also complete a demographic questionnaire about their education, employment, gender, and race (see S2 Appendix).

The number of participants was determined based on power analysis performed with G*Power 3.1 [33] for a repeated measures between-subject F-test with target effect size *f*^2^ = .1225 (medium; [34], *alpha* = .05, power = .8, number of groups (experimental conditions) = 3, number of trials = 4, and projected correlation between measurements = .5. We reasoned that compelling evidence would require at least a medium effect size of experimental condition. Based on these parameters, the required number of participants is 72. The planned analyses include Generalized Linear Mixed Model rather than an F-test. We used F-test-based effect size estimations for simplicity. The four test trials were treated as repeated measures.

Participants may be excluded and replaced due to fussiness, crying, or equipment failure. Further, because our Covid-19 Contingency Plan (see below) involves testing infants using Lookit–an online platform designed for developmental research–we expect a data loss rate of about 47–50% [35] due to infants’ crying or fussiness, parental interference, or technological issues. This, we anticipate that the total number of infants recruited could reach 140.

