#### Proportion of LT to the target

Semantic Priming condition: We predict significant effects of Condition, with average proportion of LT (across 6 s) to the target significantly higher in the Semantic Priming than in the No Priming and Follow-up Control conditions. Further, we predict that if infants successfully infer the meaning of the novel word and establish a representation of its referent in the Semantic Priming condition, their LT to the target will be significantly above chance (50%).

No Priming condition: If infants’ looking behavior is influenced by semantic inferences, rather than baseline preferences, then their LT to both objects in the No Priming condition will be equivalent and will not deviate significantly from chance. We predict this because there is no basis for infants to infer the meaning of the novel word after being presented with three semantically distant word-object pairs.

Follow-up Control condition: If infants’ looking preference in the Semantic Priming condition is the result of the semantic relations among the objects themselves, then their performance in the Follow-up Control condition will not differ from the Semantic Priming condition. Conversely, if infants’ looking in the Semantic Priming condition reflects infants’ inferences about novel word meanings, their LT in the Follow-up Control condition should not significantly deviate from chance.

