### Time course

We expect that the time course data will show significant divergences between the conditions after each verbal prompt. Based on our pilot data, we envision that after each prompt, infants in the Semantic Priming condition will exhibit increased proportion of looking to the target, which we predict to be above the chance level. In the Follow-up Control condition, infants’ looking behavior is likely to not be significantly affected by the verbal prompts because according to our hypothesis, they will have no particular expectations about the meaning of the novel word. It is, however, also possible that they will exhibit a weak preference for the target object (the object that is target in the Semantic Priming condition) based on their expectations about the next item shown given the relatedness of the three demonstrated objects. In the No Priming condition, infants have no basis to form any particular expectation about the object or the meaning of its label. For this reason, we expect that infants’ looking behavior will not be affects by the verbal prompts and remain around the chance level for the duration of the test trial.

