#### Predictions

We expect that on the comprehension task that tests infants’ knowledge of the familiar 12 words, infants will exhibit excellent performance and look to the target images over 70% of the time over the course of the trial. In the experiment proper, if 12-month-olds can indeed establish a representation of word meaning from abstract verbal reference, they should successfully map the novel word to the unseen object, echoing the results of Experiment 1. We expect to observe a significant effect of Condition on both DVs–the overall proportion of LT to the target across 6 s and the time course of infants’ LT. We predict that the direction of differences will be the same as in Experiment 1. Further, if our hypothesis is correct, then infants’ performance on the comprehension test will be correlated with their success in the experiment proper. However, if despite vocabulary training, 12-month-olds fail to learn novel words, this will either suggest that these infants cannot yet resolve abstract verbal reference, or that their sensitivity to semantic priming is insufficiently robust to guide inferences about absent objects. Additional investigations will be required to distinguish between these possibilities.

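### The stated power of .8 belongs to a three-group omnibus test that cannot separate the two rival accounts, and it does not follow from its own inputs at 72 infants; the two contrasts that carry the claim have no stated power

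*Protocol article*

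**What the plan says.** The Participants section of Experiment 1 describes a "power analysis performed with G*Power 3.1 [33] for a repeated measures between-subject F-test with target effect size" f² = .1225. The remaining inputs are "alpha* = .05, power = .8, number of groups (experimental conditions) = 3", then "number of trials = 4, and projected correlation between measurements = .5". It concludes: "Based on these parameters, the required number of participants is 72". It ties compelling evidence to a medium effect of experimental condition. It also says that the planned analysis is a mixed model and that the F-test was used for simplicity.

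The prediction for the 6-second average (Predictions, Proportion of LT to the target) is that looking to the target will be "significantly higher in the Semantic Priming than in the No Priming and Follow-up Control conditions". The Procedure section explains the role of FC. If looking is driven by the objects, FC should not differ from SP. If it reflects verbal reference, FC should not differ from NP.

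Under Time course, the plan allows for FC infants that it is "also possible that they will exhibit a weak preference for the target object". No size is given.

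The Analyses section names Condition as the fixed factor and names no contrasts. Experiment 2 uses the same groups, N and analyses (with the word-knowledge score added). Its Predictions section says "We expect to observe a significant effect of Condition on both DVs", and the next sentence adds that the differences should run in the same direction as in Experiment 1.

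**The concern.** The test that was powered and the prediction that carries the claim are different things. A significant three-group Condition effect says only that the three means are not all equal. It does not show whether FC sits with NP, as verbal reference requires, or with SP, as the object-driven account requires. FC was included to make that distinction, and the comparison that makes it, SP against FC, has no stated power.

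Two things are at stake. A reader may take the power of .8 as the chance of confirming the prediction, which it is not. And if FC infants show some preference for the target, SP and FC may fail to differ significantly even though naming has a real effect. By the logic of the Procedure section, that would count towards the object-driven account.

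**Working it through.** **Inputs from the Participants section:** f² = .1225 (f = .35), alpha .05, power .8, 3 groups, m = 4 trials, correlation ρ = .5, N = 72 (24 per group). **Assumptions not in the documents:** each contrast is two-sided at .05 with pooled error on 69 df; both must be significant in the predicted direction; FC carries a share w of the SP–NP gap.

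**1. The plan's own figure.** For the between-subject test, λ = f²·N·m / [1 + (m − 1)ρ], with 2 and N − 3 df.
- N = 72: λ = .1225 × 72 × 4 / 2.5 = 14.1; power 91.9%.
- N = 54: λ = .1225 × 54 × 4 / 2.5 = 10.6; power 81.4%.
- N = 51: power 78.9%.

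So these inputs need 54 infants for 80%, not 72. N = 72 is returned with f = .30 (81.2%) or ρ = .8 (81.3%), but neither value is stated.

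**2. What the omnibus test can tell apart.** Its power depends on the spread of the means, not on which group is high. At f = .35 and N = 72 it is 91.9% with FC = NP and 91.9% with FC = SP. In the second case both contrasts succeed in only 2.5% of studies.

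**3. Power for the two contrasts.** The SD of an infant's four-trial mean is √(2.5/4) = 0.791 trial-level SDs. The standard error of a difference between two groups is 0.791 × √(2/24) = 0.228. With means (SP, NP, FC) = d × (1, 0, w) and d set so that f = .35, d is 0.742 at w = 0. Simulated power:

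| FC share w | omnibus | SP > FC alone | both contrasts |
|---|---|---|---|
| 0 | 92% | 89% | 82% |
| .14 | 92% | 84% | 80% |
| 1/4 | 92% | 76% | 74% |
| 1/3 | 92% | 68% | 67% |
| 1/2 | 92% | 46% | 45% |

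Holding f at .35 lets the SP–NP gap grow with w. If that gap is instead fixed at 0.742, power for both contrasts is 77% at one tenth, 64% at one quarter, 55% at one third and 35% at one half.

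**4. Sensitivity to the effect size.**
- If f = .30 is the input that produced 72, power for both contrasts is 67% with FC = NP and 59% at one quarter.
- On the pilot scale (SP 64%, NP at 50%), an SD of 8% gives 98% at one third and 85% at one half.
- The pilot t does not match that SD: 14 / (8/√18) = 7.4, not 5.5. The SD implied by t = 5.5 is 14 × √18 / 5.5 = 10.8%, which gives 84% at one third and 60% at one half.

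**5. Sensitivity to sidedness.** With one-sided .05 tests and f = .35, power for both contrasts is 90% at w = 0, 84% at one quarter and 78% at one third.

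**The case against.** The strongest reply is that the plan's main prediction puts FC at chance alongside NP, and there both contrasts succeed with 82% power, above the stated level. This stands, with the limit that it holds at f = .35.

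The low figures need an intermediate FC. The plan raises that as a secondary possibility, only for the time course, and gives no size. A share of one half is hard to call weak. With f held at .35, a share up to about 14% leaves power at 80% or more. Pilot-sized effects keep it above 80% at one third with either reading of the pilot SD. A small pilot may overstate the effect, and the study was sized on f = .35, but the pilot is the only empirical evidence in the document. All this stands and limits the point.

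A reader might infer that the plan treats a significant omnibus effect as proof of verbal reference. The document does not say so. The prediction is already worded as SP above both other groups, the Procedure section gives SP against FC its proper role, and Experiment 2 also predicts the direction. What remains is that the power statement describes a test that does not make this distinction.

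Sidedness and multiplicity are commonly left to an analysis plan, so their absence is no fault in itself. Two-sided .05 is an assumption of this check.

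**Conclusion.** The point holds and is minor. The stated power describes the omnibus Condition test, which is equally likely to be significant under either account, while the claim needs SP > NP and SP > FC. The stated figure also disagrees with its own inputs: they give N = 54 for 80% and about 92% at 72.

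The documents do not support the stronger conclusion that the study is underpowered for its claim. At f = .35, power for both contrasts is about 82% if FC equals NP. A shortfall arises only with an intermediate FC (above about 14% of the SP effect with f held at .35, sooner if the SP–NP gap is held fixed) or if the design effect was really smaller than f = .35. The FC shares and the two-sided .05 rule are assumptions.

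**What to change.** Keep N = 72.

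- **Analyses and Predictions (Experiment 1) and Predictions (Experiment 2):** name SP minus NP and SP minus FC as the two planned contrasts, each two-sided at .05. No alpha split is needed, because both must succeed. State that a significant omnibus Condition effect alone does not support verbal reference.
- **Participants (Experiment 1):** first reconcile the power inputs with 72. Then state power for the two-contrast criterion with FC equal to NP, and under one or more FC levels labelled as assumptions. The 82% should not be printed before the inputs are reconciled: it belongs to f = .35, and at f = .30 the figure is 67%.

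The cost is wording only, with no extra infants or data. The downside is that the stated power looks less favourable if FC shows a weak preference. Data collection is planned to follow in-principle acceptance, so the change can be made before any data are seen.

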#### Pilot data

The results of the pilot data analyses (*N* = 18) in the Semantic Priming condition reveal a significant looking preference for the target. Infants’ LT to the target image across 6 s was significantly above chance (50%), *M* = 64%, *SD* = 8%, *t*(17) = 5.5, *p* < .001. The time course data reflects infants’ reactions to verbal prompts: infants’ looking to the target increased after each mention of the target word (Fig 3). These data provide assurances that the task is well-suited to test 15-month-olds’ ability to learn novel word meanings from displaced reference and provides hints that infants might indeed be using semantic priming to infer such meanings.

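### The listed power inputs give 54 infants (18 per condition), not 72, and the pilot mean, SD and t cannot all be right

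*Protocol article*

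**What the plan says.** Participants (Experiment 1) names the software, the test and all inputs. The calculation is "for a repeated measures between-subject F-test with target effect size" f² = .1225, with "alpha* = .05, power = .8", and "number of groups (experimental conditions) = 3, number of trials = 4, and projected correlation between measurements = .5". It ends: "Based on these parameters, the required number of participants is 72". The section adds that a generalized linear mixed model is planned and that the F-test stands in for it for simplicity. Excluded infants may be replaced, and with online data loss of about 47–50% total recruitment could reach 140.

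Experiment 2 also plans 72 infants, 24 per condition, and gives no separate calculation.

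Pilot data reports, for 18 infants in the Semantic Priming condition tested against 50%: "M* = 64%, *SD* = 8%, *t*(17) = 5.5", with p < .001.

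**The concern.** The sample size is presented as the direct output of a calculation whose inputs are all printed, so a reader can rerun it. The rerun does not return 72. This sentence is the only justification of N in a registered report, and it carries over to Experiment 2. As printed, the target effect, the power and the N do not belong together, so a reader cannot tell which effect the study was sized to detect.

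The pilot summary has a similar fault: its mean, SD and t are linked by a simple formula that the printed values do not satisfy. It does not feed into the sample size, but the article uses it as assurance that the task works and as the basis for expecting success in Experiment 1.

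**Working it through.** **1. Sample size from the stated inputs**

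Inputs, all from Participants (Experiment 1): f² = .1225 (so f = .35), alpha = .05, power = .80, k = 3 groups, m = 4 trials, correlation r = .5.

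For the between-subject factor in a repeated-measures design, the noncentrality parameter is

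λ = f² · N · m / (1 + (m − 1) r) = .1225 · N · 4 / (1 + 3 × .5) = .196 N,

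and power is the probability that a noncentral F with 2 and N − 3 degrees of freedom exceeds the 5% critical value of the central F.

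| N | λ | Power |
|---|---|---|
| 51 | 10.00 | .789 |
| 52 | 10.19 | .798 |
| 53 | 10.39 | .806 |
| 54 | 10.58 | .814 |
| 72 | 14.11 | .919 |

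The smallest N reaching .80 is 53, or 54 (18 per condition) with equal groups. The printed 72 is 18 infants more, and its power is about 12 points above the stated .80. Solving for power = .80 at N = 72 gives f² = .087 (f = .296).

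**2. Attempts to reproduce 72**

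Other tests on the same inputs (balanced N, except the regression):

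- within-subject factor: 15
- within-between interaction: 18
- one-way ANOVA with no repeated measures: 84
- trials treated as independent: 21
- regression f² test with 2 predictors: 82

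Other readings of .1225:

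- as f: 405
- as η²: 48
- as f² before conversion to f²/(1 + f²): 60

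Raising power to .90 gives 69.

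A result of exactly 72 appeared only when a stated input was changed or an unstated one added:

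- f = .30 (power .812 at N = 72, .794 at 69)
- r = .8 (power .813 at N = 72, .794 at 69)
- 6 groups
- inflation of 54 for 25% loss: 54 / .75 = 72

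The article does not give a 25% loss rate. Its own loss rates are applied to 72: 72 / (1 − .47) = 136 and 72 / (1 − .50) = 144, which bracket the stated 140. So 72 is the number to be analysed, before any allowance for loss.

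**3. Pilot statistic**

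Inputs from Pilot data: M = 64%, SD = 8%, n = 18, reference value 50%.

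t = (64 − 50) / (8 / √18) = 14 / 1.886 = 7.42.

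Rounding of M and SD allows 13.5 / (8.5 / √18) = 6.7 up to 14.5 / (7.5 / √18) = 8.2, so 5.5 is out of reach. Working back from t = 5.5:

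- with M = 64%, SD = 14 × √18 / 5.5 = 10.8%
- with SD = 8%, M = 50 + 5.5 × 8 / √18 = 60.4%

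On 17 degrees of freedom, both t = 5.5 and t = 7.4 give p < .001.

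**The case against.** The strongest reply is that the discrepancy is in the safe direction. At the stated effect, 72 infants give more power than claimed, nothing in the conduct of either experiment changes, and the article already says that the F-test is a simplification. The team may also have rounded up deliberately. The first part stands, and it limits the point to a reporting error. But the simplification explains why an F-test was used, not why that F-test returns 72. A deliberate margin cannot be excluded, but the sentence presents 72 as what the inputs require.

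A reader might infer several stronger things that the document does not support:

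- *That 54 would be enough.* The figure of 54 is for the omnibus F-test only. It says nothing about the mixed model with Test Item as a random factor, the contrasts or the predictions of no difference.
- *That the calculation belongs to another design.* The 3 groups, 4 trials and 24 per condition all match the Procedure. Only the step from inputs to N fails.
- *That an input was certainly misreported.* The resulting N could be the misreported figure instead.
- *That a null result would be read with power the study lacks.* At f = .35 the omnibus test has more power than stated.
- *That the prediction of looking "significantly higher in the Semantic Priming than in the No Priming and Follow-up Control conditions" is underpowered.* Power for two contrasts depends on assumptions the article does not state, such as equal controls and unadjusted tests. Under those two assumptions the joint power at f = .35 is about 82%, so no shortfall against 80% is shown.
- *That the pilot SD is the wrong figure.* The mean or the t could equally be the misprint.

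**Conclusion.** The sample-size derivation is wrong as written. The stated inputs give 53 infants (54 balanced), not 72; at 72 they give about 92% power for the omnibus Condition effect, and 80% power corresponds to f² = .087 instead of .1225. The document does not show which figure is at fault.

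These values rest on the article's own test and inputs, and on four usable trials per infant. Data preparation drops trials with under 1 s of looking, and on the same formula power at 72 is about 90% with three trials per infant and 86% with two. The 92% is therefore an approximation to the planned analysis.

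The pilot inconsistency is a separate reporting error (7.4 against 5.5). It leaves the p < .001 conclusion intact and does not affect N.

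**What to change.** Keep 72 in both experiments and correct the text in one of two ways.

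- If the calculation was run with another input, print that input.
- Otherwise replace the sentence with, for example: *These inputs require 54 infants. We enrol 72 (24 per condition), which gives about 92% power for the omnibus F-test at f² = .1225 and 80% power at f² = .087. This is an F-test approximation to the planned mixed model and assumes four usable trials per infant.*

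Carry the same statement to Participants in Experiment 2.

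In Pilot data, recompute the mean, SD and t from the pilot records and correct whichever is wrong.

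The cost is a text correction and one check of the pilot data, with no change to recruitment, procedure or analysis.
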